## Abstract

**Background:**

Chronic kidney disease (CKD) is a relatively newly recognised but common long-term condition affecting 5 to 10% of the population. Effective management of CKD, with emphasis on strict blood pressure (BP) control, reduces cardiovascular risk and slows the progression of CKD. There is currently an unprecedented rise in referral to specialist renal services, which are often located in tertiary centres, inconvenient for patients, and wasteful of resources. National and international CKD guidelines include quality targets for primary care. However, there have been no rigorous evaluations of strategies to implement these guidelines. This study aims to test whether quality improvement interventions improve primary care management of elevated BP in CKD, reduce cardiovascular risk, and slow renal disease progression

**Design:**

Cluster randomised controlled trial (CRT)

**Methods:**

This three-armed CRT compares two well-established quality improvement interventions with usual practice. The two interventions comprise: provision of clinical practice guidelines with prompts and audit-based education.

The study population will be all individuals with CKD from general practices in eight localities across England. Randomisation will take place at the level of the general practices. The intended sample (three arms of 25 practices) powers the study to detect a 3 mmHg difference in systolic BP between the different quality improvement interventions. An additional 10 practices per arm will receive a questionnaire to measure any change in confidence in managing CKD. Follow up will take place over two years. Outcomes will be measured using anonymised routinely collected data extracted from practice computer systems. Our primary outcome measure will be reduction of systolic BP in people with CKD and hypertension at two years. Secondary outcomes will include biomedical outcomes and markers of quality, including practitioner confidence in managing CKD.

A small group of practices (n = 4) will take part in an in-depth process evaluation. We will use time series data to examine the natural history of CKD in the community. Finally, we will conduct an economic evaluation based on a comparison of the cost effectiveness of each intervention.

**Clinical Trials Registration:**

ISRCTN56023731. ClinicalTrials.gov identifier.

## Background

Chronic kidney disease (CKD) is a common long-term condition, affecting 5 to 10% of the population. CKD is an independent risk factor for cardiovascular disease, established renal failure (ERF) and all cause mortality [1-3]. Patients with CKD are far more likely to die prematurely from cardiovascular disease than progress to ERF requiring dialysis or transplantation. The presence of proteinuria confers additional cardiovascular risk.

CKD is classified into five stages based upon a measurement of kidney function and the estimated glomerular filtration rate (eGFR) determines the class of CKD for the more severe stages (Stage three to five). Stage one and two are the mildest of the five stages of CKD and require evidence of kidney damage, usually the presence of proteinuria, to confirm the diagnosis. Stages three to five CKD can be diagnosed by eGFR alone; and stage three is now often split into stages 3a and 3b, as there are far higher rates of cardiovascular co-morbidity in stage 3b disease. People with cardiovascular co-morbidities especially hypertension and diabetes; cardiovascular risk factors, particularly raised systolic blood pressure (BP); and more specific renovascular risk factors: proteinuria and anaemia are at increased risk.

There is a broad and evidence-informed consensus that lowering BP is of central importance, both to slow the progression of CKD and reduce cardiovascular risk. Lowering of BP using angiotensin modulating anti-hypertensives, angiotensin converting enzyme inhibitors (ACEI) and angiotensin (II) receptor blockers (ARB) appears to have additive renal-protective benefits [4]. Strict management of BP, cardiovascular and specific renovascular risk should be feasible in primary care. Guidelines on the management of CKD have recently been published by the National Institute for Health and Clinical Excellence (NICE) [4]. In the absence of proteinuria, the threshold for intervention is a BP of ≥ 140/90 mmHg is recommended, with a target systolic BP of between 130 and 139 mmHg. In diabetes and where significant proteinuria is present, the respective values are 130/80 mmHg with a systolic target of between 120 and 129 mmHg. However these targets frequently remain unmet. Studies have demonstrated a need to improve both information and training available to practitioners with the aim of enabling them to improve the quality of care currently provided [5].

There is limited knowledge and experience of managing this condition in primary care, and while CKD has been included as one of the financially incentivised chronic disease management targets for general practice – the 'Quality and Outcomes Framework' (QOF) it is the only QOF indicator to be accompanied by a 'Frequently Asked Questions' document – requested by the British Medical Association as a condition for the inclusion of this indicator in the QOF indicator set [6]. Feedback to the investigators has been that practitioners lack confidence in the management of this condition, especially implementing the BP targets in elderly patients (who are at higher risk of CKD and its sequelae).

There are further problems with the QOF. The use of routinely collected clinical data for purposes other than clinical care may distort data recording [7]. Practitioners feel reluctant to include a patient with incomplete data on a QOF disease register as this might affect their income. Regardless, the prevalence of CKD reported through the QOF to the NHS Information Centre for 2006/7 [8] is less than half that reported in the epidemiological studies quoted in this introduction. There is *de facto *a quality gap as those people with CKD not on the disease register will not be recalled for BP and other checks.

Finally, the new NICE guidance looks at CKD at a point in time [4]. Management is largely determined by the eGFR over a three-month period, BP control and the presence or absence of proteinuria. Although there is a heuristic for a rate of decline that would trigger referral, there is dissonance between this heuristic and clinical practice in primary care. Many elderly people with CKD, even more advanced stage four disease, appear to be stable and the NICE along with previous guidance may be over aggressive for this group of patients; this may be part of the reason why clinicians are not implementing recommended BP targets [9,10]. Further research is needed to understand the natural history of the disease and whether rate of decline would be a more appropriate primary variable to detect people at risk.

### The quality of general practice computer data

UK general practice is almost universally computerised and has some of the most advanced general practice computing [11,12]; providing a rationale for the use of routinely collected data to measure the impact of the quality improvement interventions being developed and tested in this programme of research. Six factors contribute to the high quality of general practice computer data: we have an accurate denominator [13]; prescribing records are largely complete; electronic connections to laboratories mean that pathology data are complete; the QOF has improved data quality in CKD and its cardiovascular co-morbidities including diabetes; an electronic referral system has improved data quality; and the NHS has sponsored the development of a tool called MIQUEST (Morbidity Information Query and Export Syntax) to extract anonymised data – a tool we have over 10 years experience of using [14,15].

Optimal management of CKD in primary care is currently limited by a lack of knowledge about how to increase adherence to guidelines for best practice [16]. There is no single perfect quality improvement strategy to use in primary care [17]. The most commonly used strategy is dissemination of clinical practice guidelines with prompts [18]. This usually involves distribution of paper guidance and reminders with internet resources providing additional information and support. More expensive and complex interventions have been widely used, including audit-based education (ABE) where practitioners compare their own practice's adherence to guidance with that of peer practices [19,20]. Our experience from observational work has been that ABE is more effective in its second year [21]; a similar pattern is seen with using feedback to improve data quality [22].

## Methods

### Study aims and objectives

This study aims to improve the quality of CKD management in primary care with the emphasis on strict control of systolic BP to reduce cardiovascular risk and slow renal progression.

### Objectives

1. To lower the BP of hypertensive individuals with CKD to an agreed target.

2. To measure the impact of the quality improvement interventions on the recording and control of renovascular risk factors, including proteinuria; and cardiovascular co-morbidities, including diabetes mellitus.

3. To evaluate the quality improvement interventions and measure their impact on other markers of quality, including practitioner confidence.

4. To establish a cost model for each quality improvement intervention.

5. To characterise the natural history of CKD. We wish to compare those who have progressive (as defined by a yearly decrease in eGFR of >5 ml/min/1.73 m^2 ^in one year or >10 ml/min/1.73 m^2 ^in 5 years) [4], compared with non-progressive renal disease; comparing demographics, co-morbidities (including diabetes), and biomedical variables.

6. To develop improved primary care guidelines for management of CKD and measure adherence to this guidance; with an emphasis on comparing progressive, with non-progressive CKD.

### Study design

#### Study design overview

We plan to conduct a two-year, three-arm cluster randomised trial. We are carrying out a cluster randomised trial because we feel that quality improvement is often adopted at the level of the practice. A trial of individual patients would be much more difficult because it may be impossible to stop contamination between general practitioners (GPs) and other health professionals working in the same practice; GPs may see successive patients from different arms of the trial; and communication between patients randomised to different arms of the trial might also bias results.

The study has two components: a core cluster randomised trial (CRT) of 75 practices, and a parallel process evaluation and measure of how GP confidence changes over time. The core study is a three-arm CRT of 75 practices. These 75 practices are randomised into three arms of 25 practices comparing usual practice, guidelines and prompts (GaP), and ABE. This sample size is needed to show a difference of 3 mmHg in systolic BP (Figure 1). There is also a parallel study that contains additional practices: four practices form our in-depth process evaluation practices, and two testing each active intervention. Additionally, 10 practices in each arm of the study will complete a confidence questionnaire to assess if/how practitioner confidence changes in the different arms of the study (Figure 2).

**Figure 1 F1:**
[figure not shown]
The core study sample: a three-arm cluster randomised trial comparing Usual practice with Guidelines and Prompts (GaP) and Audit-based Education (ABE).

**Figure 2 F2:**
[figure not shown]
**The greater study contains the core CRT with 25 practices in each arm.** In addition there are 10 confidence questionnaire practices per arm and two in-depth process analysis practices in each of the active study arms.

However, the parallel study (Figure 2) contains two other elements:

1. Four in-depth process evaluation practices: These practices will take part in our diagnostic analysis process at the start of the study proper (*i.e*., does the intervention meet their perceived needs, and does it address barriers to quality improvement). They will validate our questionnaire to assess confidence and, during the study proper, report on the intervention exposure (*i.e*., to what extent the intended recipients are exposed to the interventions); and programme fidelity (*i.e*., whether the quality improvement intervention is delivered as planned). Two practices will give in-depth feedback about the GaP intervention and two about ABE. We will use focus groups run in each practice as our principal method of data collection; however we also plan a mid-study workshop of all the in-depth process evaluation practices. Our sample will include at least one practice from the north and from the south; we intend to recruit inner city, suburban, and county town practices; we want to see the four major brands of general practice computer systems represented across the practices so that we can also test our queries and data extracts.

2. An additional 10 practices in each arm will complete a confidence questionnaire: We will recruit 10 additional practices in each arm that will participate in the study but also complete a questionnaire about their confidence in the management of CKD. We are primarily doing this to assess if any of the interventions have a greater effect on confidence. We are sending this questionnaire to a separate group of practices because completing the questionnaire may be an intervention in its own right, possibly as great as GaP. We will be able to compare questionnaire and non-questionnaire practices in each arm at the end of the study.

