##### Usual practice

These practices will be allocated to this arm at randomisation (n = 35 practices – 25 in the core CRT and 10 in the questionnaire group). Once assigned to this arm, a minimum of contacts will be made of these practices other than for data collection.

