### Randomisation

#### Randomisation was conducted in blocks

Practices agree to participate in the study the basis that they will be assigned at random to an arm of the study. We excluded practices who wanted to choose an arm of the study. They are assigned their arm by simple random allocation. Randomisation will be performed with a table of random numbers by [name]; in the order practices complete their consent to participate. He allocates, at random, recruited practices in blocks of nine; accepting that there will be a final block of less than nine.

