#### Allocation concealment

The allocation is not shared with those who will be involved in the data analysis. The clinical data collected are identical in all three arms of the study, so there should be no clues within these data as to which arm is which. The allocated arm is recorded in our database of practice details that is kept entirely separately from the pseudonymised table of data used for analysis. Within the analysis table the practices in each of the three arms are identifiable for analysis – but there is no labelling of which specific arm any practice is allocated to. Similarly, patient and practice identifiers are pseudonymised, which again makes it harder for the analysts to identify individual arms.

Ten practices in each arm are labelled as having had the questionnaire. The four in-depth process evaluation practices have a separate series of identification numbers so that they can have their data analysed but excluded from the study.

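### No random assignment of the confidence questionnaire is stated, so the within-arm comparison of questionnaire and non-questionnaire practices has no stated protection from selection

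*Protocol article*

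**What the plan says.** All of this is in the protocol article.

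- **Study design overview, parallel study, item 2 (below Figure 2).** The questionnaire group is described as: "We will recruit 10 additional practices in each arm that will participate in the study but also complete a questionnaire". It is kept apart from the core trial because "completing the questionnaire may be an intervention in its own right, possibly as great as GaP". The item closes by offering a comparison: "We will be able to compare questionnaire and non-questionnaire practices in each arm at the end of the study".
- **Usual practice (Interventions).** The arm is counted as "n = 35 practices – 25 in the core CRT and 10 in the questionnaire group", and all of these practices are said to enter the arm at randomisation. The sections on the other two arms give the same 25 plus 10.
- **Randomisation.** "They are assigned their arm by simple random allocation", "in the order practices complete their consent to participate". The section adds: "He allocates, at random, recruited practices in blocks of nine". Arm is the only thing it allocates.
- **Allocation concealment.** "Ten practices in each arm are labelled as having had the questionnaire". No rule for choosing the ten is given.
- **Diagnostic analysis and process evaluation (outcomes).** Confidence is measured at baseline and at 18 months.

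**The concern.** The article treats the questionnaire as a possible exposure of the same order as one of the trial's two active interventions. It then says that exposed and unexposed practices can be compared within each arm. Such a comparison isolates the questionnaire only if the two groups would otherwise be alike, and random assignment is what would secure that. The text describes extra recruitment and a label.

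The Recruitment section lists several routes into the study: research networks, teaching networks in particular areas, word of mouth, and spread from practice to practice. The Discussion names the September 2008 NICE guidance and the QOF indicator as outside pressures that might exceed any study effect, and takes comfort that they act equally on all three arms. That comfort covers the arms. It does not extend to questionnaire against core practices within an arm, should the two groups have entered by different routes or at different times.

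At stake is one secondary result. If questionnaire practices ended with different blood pressure or recording, the reader could not tell a questionnaire effect from a difference in the kind of practice that received it.

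**Working it through.** **Inputs.** SD of practice means 3.77 mmHg, target difference 3 mmHg, 5% level, 80% power, 25 practices per arm (Cluster randomised trial sample size). 10 questionnaire and 25 core practices per arm (Interventions), hence 30 and 75 over three arms. Two-sided testing and a normal approximation are assumed.

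**1. The plan's own figure.** n per arm = 2 × (1.960 + 0.842)² × 3.77² / 3² = 24.8, rounded up to 25. This reproduces the stated 25 (power 80.3%). Nothing here disputes that figure.

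**2. What is randomised.**

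| Feature | Stated mechanism |
|---|---|
| Arm, all 35 practices | Random, in consent order |
| Questionnaire or not, within arm | Additional recruitment, then a label; no random rule stated |

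**3. Precision of the offered comparison.** SE = 3.77 × √(1/n₁ + 1/n₂).

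- Within an arm: 3.77 × √(1/10 + 1/25) = 1.41 mmHg.
- Pooled over arms: 3.77 × √(1/30 + 1/75) = 0.81 mmHg.

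**4. Effect of a group difference unrelated to the questionnaire.** The article gives no such figure, so 1 and 2 mmHg are assumptions. The false-positive rate is the chance that a two-sided 5% test declares a questionnaire effect when there is none.

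| Assumed difference | Within arm | Pooled |
|---|---|---|
| 0 | 5% | 5% |
| 1 mmHg | 1/1.41 = 0.7 SE; 11% | 1/0.81 = 1.2 SE; 23% |
| 2 mmHg | 2/1.41 = 1.4 SE; 29% | 2/0.81 = 2.5 SE; 69% |

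**5. What randomising the questionnaire would give.** With the same SD, power for 3 mmHg would be 57% within an arm and 96% pooled. The smallest difference detectable with 80% power is 2.80 × 1.41 = 4.0 mmHg within an arm and 2.80 × 0.81 = 2.3 mmHg pooled. Pooling assumes a similar questionnaire effect in each arm.

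**Limit of the figures.** The 3.77 mmHg describes practice mean levels, while the outcome is change in systolic pressure. The article gives no SD for change, so steps 3 to 5 show scale only.

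**The case against.** The strongest reply is that the article is silent on how the ten are chosen, and silence does not show a non-random choice. A reader might infer that the questionnaire practices are a later or differently recruited wave. The documents do not support that: additional may mean only 10 on top of 25, no recruitment route is tied to questionnaire status, there is one set of inclusion criteria, and all 35 practices go through one arm allocation. A random draw is neither stated nor excluded, and a condensed article may leave such a rule to the full protocol.

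Other parts of the reply also stand:

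- The comparison is offered as something the study will be able to do. The statistical analysis sections do not list it.
- The group's main purpose is to measure confidence between arms. Keeping it separate shields the core trial from the questionnaire however the ten were chosen.
- The 1 to 2 mmHg is assumed. Within an arm, which is how the article frames the comparison, even 2 mmHg is only 1.4 standard errors. A stable difference in level would largely cancel in an analysis of change.

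What the reply does not remove is that the article does describe a mechanism. It sets out arm allocation step by step, says the questionnaire group is formed by recruitment, and then offers a comparison which that mechanism does not protect. Putting all 35 practices through randomisation settles their arm and leaves open which ten receive the questionnaire.

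**Conclusion.** The point holds in a limited form. As written, random allocation covers the arm, questionnaire status has no stated random assignment, and the within-arm comparison could confound the questionnaire with how practices came to be in each group. The possible distortion cannot be sized from the article. Under the assumed 1 to 2 mmHg it is 0.7 to 1.4 standard errors within an arm and 1.2 to 2.5 pooled, using an SD for levels.

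Two stronger readings should be resisted. A reader might infer that the comparison of confidence between arms is compromised; it is not, because arm is randomised for all 35 practices and nothing suggests that the ten are chosen differently from arm to arm. A reader might also infer a threat to the primary outcome; a comparison restricted to the 25 core practices per arm, on which the trial is powered, is not affected.

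It is still worth correcting, since the article itself rates the questionnaire as possibly equal to an active arm and the remedy is nearly free.

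**What to change.** Amend item 2 of the parallel study and the Randomisation section to say that all 35 practices per arm are recruited as one pool, and that 10 of the 35 in each arm are drawn at random for the questionnaire at allocation, before the baseline questionnaire is sent. The random-number table already in use would serve: mark 10 of the 35 positions in each arm's sequence in advance.

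The Randomisation section is partly in the past tense, so some practices may already have been designated. If that was done by any route other than a random draw, state that the questionnaire against non-questionnaire comparison is non-randomised and exploratory.

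The cost is one extra random draw and a sentence or two of text, with no extra practices and no change to the core sample size.

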#### Participants

The participants are GPs located in practices (our clusters) across England. We aim to recruit a nationally representative sample of practices from: in and around London – especially inner city and suburban southwest London; urban and rural Surrey and Sussex; Leicester city and surrounding areas; Birmingham inner city and suburban; and Cambridge. The locality structure is pragmatic because groups of practices need to come together for the ABE workshops. An inclusion criteria for a locality is that their local renal unit would support the workshop within their locality and review the GaP to minimise any conflict with local policy.

The primary research participants are GPs involved in the study who will receive the quality improvement interventions listed below. The interventions will be implemented at the practice (cluster) rather than the individual level. The study subjects (who may be regarded as secondary participants) will be all individuals with CKD within the study practices. CKD will be defined using the internationally accepted National Kidney Foundation (NKF) definition [23] using two measures of eGFR of less than 60 ml/min/1.73 m^2 ^at least three months apart. However, we will also explore the effects of including people with a single recording of eGFR.

The participants do not receive any financial incentives to participate, though they do receive financial compensation for the time actually spent attending study activities. These will vary according to the arm of the study they are allocated to.

